### Control

The aim of the trial is to compare the effects of an exercise program with routine care rather than to test a specific type of exercise. Thus, the control group is a routine care control group, which commonly implies brief verbal, general information about the benefits of physical activity from the treating physicians or breast cancer nurses. Participation in voluntary training groups organised by the treating hospital is not encouraged for participants since this implies that physical activity is potentially increased to the level specified in exclusion criteria. It is important to acknowledge that individuals consenting to an exercise trial may be more predisposed to exercising and may thus continue performing physical exercise if they are allocated to the control group. To measure this potential effect, all physical activity of both groups will be digitally collected so any “contamination” in the control group can be accounted for in the analysis. Importantly, the trial pursues an active recruitment strategy in order to meet potential participants at their respective fitness level however little they may be used to exercise. The control group will not have access to trial-specific exercises via the mobile application.

##

## Outcomes, Variables and measures

The **primary endpoint** pCR is measured by histopathological assessment according to the TNM classification of the American Joint Committee on Cancer (ypT0/is ypN0) after breast and axillary surgery (approx. 5 months after initiation of NACT, according to standard of care).

In order to ensure congruence in assessment of pCR between study sites, a central review of histopathological tumour slides will be performed for all included cases. Routine slides will be collected from participating sites and digitally scanned for central pathology review at Karolinska University Hospital in Stockholm. Slides will thereafter be returned to the study sites.

The **secondary** endpoints are:

1. Residual Cancer Burden (RCB), calculated using primary tumour bed area (mm x mm), overall cancer cellularity (%), percentage of cancer that is in situ disease (%), number of positive lymph nodes and diameter of largest nodal metastasis (<http://www3.mdanderson.org/app/medcalc/index.cfm?pagename=jsconvert3>). Categories are RCB-0 (pCR), RCB-I, RCB-II and RC-III.
2. Objective tumour response according to RECIST criteria^31^, measured as % change from largest radiological diameter of target lesion at baseline to pre-surgery (mammography or magnetic resonance tomography). No more than two target lesion are measured, which are the largest measurable lesions within the breast. Categories are: complete response (CR, disappearance of all target lesions), partial response (PR, at least a 30% decrease in the sum of the largest diameter (LD) of target lesions, taking as reference the baseline sum LD), progressive disease (PD, at least a 20% increase in the sum of the LD of target lesions, taking as reference the smallest sum LD recorded since the treatment started or the appearance of one or more new lesions) and stable disease (SD, neither sufficient shrinkage to qualify for PR nor sufficient increase to qualify for PD, taking as reference the smallest sum LD since the treatment started).
3. Overall, breast cancer-specific and recurrence-free survival at 2, 5 and 10 years. For overall survival, censuring is at death or at date for latest follow-up. For breast cancer-specific survival, censuring is at breast cancer-specific death or at date of last follow-up. For recurrence-free survival, censuring is at first local, regional or distant recurrence or at death or date of last follow-up. Contralateral invasive or in situ breast cancer or non-breast secondary malignancies are not counted as an event, in accordance with STEEP criteria^32^.
4. Health-related quality of life including fatigue, assessed by the EORTC QLQ-C30 and BR23 questionnaires (baseline, pre-surgery, 1- and 2-year follow-up)
5. Self-reported physical activity (Modified Godin Leisure Time Physical activity questionnaire) at baseline, pre-surgery, and 1- and 2-year follow-up, facilitating subsequent adjustment for any cross-contamination in the control group
6. Toxicity-related outcomes:
   1. Chemotherapy completion rates, i.e. the proportion of participants receiving the planned number of treatments at full dosage regarding neoadjuvant chemotherapy (measured pre-surgery).
   2. Number of unplanned hospital admissions during neoadjuvant chemotherapy.
   3. Objective cognitive dysfunction measured by an online neuropsychological test (Amsterdam Cognition Scan)^33^ (baseline and 1-year follow-up).
   4. Cardiac toxicity (defined as either left ventricular ejection fraction (LVEF) decline >15% or LVEF decline below an absolute value of 50% or clinical heart failure), to be measured by echocardiogram at baseline and after 3 months of NACT in the HER2-positive subgroup
   5. Sick leave (patient-reported percentage of sick leave as a single measurement pre-surgery and at 1- and 2-year follow-up)
7. Device-measured physical activity level and resting heart rate assessed through the Fitbit activity tracker (baseline to 1-year follow-up).
8. Muscle strength assessed through the handgrip strength test and hypothetical 1-RM maximal leg muscle strength tests (baseline and pre-surgery).
9. Cardiorespiratory fitness assessed by the Ekblom-Bak submaximal cycle test (baseline and pre-surgery).

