## Study calendar

| ***Time point*** |  | |
| --- | --- | --- |
| Baseline (before initiation of NACT) | - Verify eligibility - Informed consent - Three 14G tumour biopsies in addition to diagnostic biopsy* - Blood and plasma samples (4-5 x 10 ml) * - Faeces samples * - Full tumour biology (ER, PR, HER2, tumour grade, and Ki67)   Baseline questionnaires and testing   1. EORTC QLQ-C30 (quality of life) 2. EORTC QLQ-B23 (quality of life, breast cancer) 3. Sense of coherence (SOC-13) 4. Godin Leisure Time Self-Reported Physical Activity questionnaire 5. Self-Efficacy of Exercise (SEE) questionnaire 6. Hand grip muscle strength test 7. 1-RM leg press test 8. Ekblom-Bak submaximal cardiorespiratory cycle test 9. Amsterdam Cognition Scan 10. BMI, body fat composition, haemoglobin levels, blood pressure, demographics and medical history | |
| **Randomization** | ***Standard*: Usual care**  ***Intervention*: Physical exercise intervention** | |
| Pre-surgery | Repeat baseline questionnaires and testing (1.-2., 4.-8., 10.)  Device-measured physical activity (Fitbit activity tracker)  Blood (4-5 x 10 ml) and faeces samples *.  Record toxicity-related outcomes and treatment details (CRF) | |
| Surgery | Breast and axillary surgery: endpoint pCR assessed and recorded.  Tumour tissue collected and stored at trial biobank* | |
| Postoperative treatment | Adjuvant treatment as per clinical routine | |
| **Follow-up (years after surgery)** | **1** | **2** |
| EORTC QLQ-C30* | x | x |
| EORTC QLQ-B23* | x | x |
| Record recurrence and survival | x | x |
| Godin (physical activity)* | x | x |
| SEE scale | x |  |
| Amsterdam Cognition Scan | x |  |
| Faeces sample * | x |  |
| Device-measured physical activity (Fitbit activity tracker) | x |  |
| Self-reported sick leave | x | x |

* Stockholm sites only

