#### Secondary endpoints

1. *Residual Cancer Burden (RCB)*

Residual Cancer Burden (RCB) is measured as four ordered categories (RCB-0 which corresponds to pCR, RCB-I, RCB-II, and RC-III) at histopathological assessment of the surgical specimen. An ordinal regression model, adjusting for biological tumour type (stratification factor in the randomization), will be used to analyse differences between the treatment arms. If the proportional odds assumption of the model is violated, a nominal regression model or a generalized logistic model will be used instead if appropriate.

1. *Objective tumour response*

Response Evaluation Criteria in Solid Tumours (RECIST) will be applied in order to assess change in radiological tumour size (%) from baseline to pre-surgery imaging. RECIST criteria classify response into four ordinal outcome categories: complete response, partial response, stable disease and progressive disease (see page 18)^31^. An ordinal regression model, adjusting for biological tumour type (stratification factor in the randomization), will be used to analyse differences between the treatment arms. If the proportional odds assumption of the model is violated, a nominal regression model or a generalized logistic model will be used instead if appropriate. Tumour size at histopathological assessment of the surgical specimen may be included in comparative analyses. Mean difference in reduction of tumour size between treatment arms will be analysed with an ANOVA, including biological subtype as a factor in the model.

1. *Survival outcomes*

All-cause, breast cancer-specific and recurrence-free survival will be analysed at 2, 5 and 10 years. Contralateral breast cancer is not regarded an event. Difference in time-to-event outcomes between treatment arms will be compared. The mortality outcomes are defined as time from date of randomisation to death (from any cause or breast cancer as underlying cause, respectively) or censoring at end of follow-up. For recurrence-free survival, the outcome is measured as time from date of randomisation to breast cancer relapse or censoring at end of follow-up. Survival estimates after 2, 5 and 10 years of follow-up will be compared using Kaplan-Meier estimates. Furthermore, a Cox regression model, adjusting for biological subtype will also be used.

1. *Health-related quality of life*

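### Progressive and stable disease are referenced to an on-treatment minimum that a baseline-to-pre-surgery comparison does not supply

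*Protocol*

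**What the plan says.** In the Protocol, section Outcomes, Variables and measures, secondary endpoint 2 is objective tumour response by RECIST, "measured as % change from largest radiological diameter of target lesion at baseline to pre-surgery (mammography or magnetic resonance tomography". The analysis text under Secondary endpoints repeats the two-point design: RECIST is applied "in order to assess change in radiological tumour size (%) from baseline to pre-surgery imaging". The Study calendar places baseline before the start of neoadjuvant chemotherapy and lists no tumour imaging at any visit.

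The categories use two different references:

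- Partial response: "at least a 30% decrease in the sum of the largest diameter (LD) of target lesions, taking as reference the baseline sum LD".
- Progressive disease by size: "at least a 20% increase in the sum of the LD of target lesions". The comparator for that growth is worded as "taking as reference the smallest sum LD recorded since the treatment started". A second route needs no comparator: "or the appearance of one or more new lesions".
- Stable disease: "neither sufficient shrinkage to qualify for PR nor sufficient increase to qualify for PD, taking as reference the smallest sum LD since the treatment started".

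Complete response needs no reference, since it is the disappearance of all target lesions. The four categories go into an ordinal regression adjusted for biological tumour type. Reduction in tumour size is analysed separately by ANOVA with biological subtype as a factor.

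**The concern.** A minimum-since-start reference suits serial imaging, where it detects regrowth after an initial response. This endpoint has no series. Its only foreseen measurement after treatment starts is the pre-surgery image, so on the wording as it stands that image is compared with itself. Progression by size then cannot occur, and marked growth is pooled with no change.

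If a site happens to record an interim scan, the opposite difficulty arises. Partial response looks back to baseline and progression looks back to the minimum, so one patient can satisfy both. The category would then depend on local scanning practice and on an unstated choice by the assessor.

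At stake is the bottom of the ordinal scale in one named secondary endpoint. The ordinal model could lose the distinction between its two worst categories, or receive categories assigned differently from site to site.

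**Working it through.** The plan states no figure for this endpoint, so there is none to reproduce. Its sample size (712, or 790 with drop-out) concerns pathological complete response and does not enter here.

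**Inputs, all from Outcomes, Variables and measures:** partial response at -30% or lower against baseline; progression at +20% or higher against the reference sum, or a new lesion; stable disease otherwise. Timing of baseline is from the Study calendar. The diameters below are illustrations.

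**Formulas.** Change on baseline = (pre-surgery - baseline) / baseline. Increase on reference = (pre-surgery - reference) / reference.

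**Three readings of the reference for progression:**

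- A, literal: smallest sum after treatment start.
- B: smallest sum with baseline counted.
- C: baseline only.

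No new lesion is assumed.

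| Course (mm) | Change on baseline | A | B | C |
|---|---|---|---|---|
| 30, 36 | +20% | 0%: stable | +20%: progression | progression |
| 30, 40 | +33% | 0%: stable | +33%: progression | progression |
| 30, 45 | +50% | 0%: stable | +50%: progression | progression |
| 30, 60 | +100% | 0%: stable | +100%: progression | progression |
| 30, 30 | 0% | stable | stable | stable |
| 30, 21 | -30% | partial response | partial response | partial response |
| 40, 20, 25 (interim scan recorded) | -37.5% | +25%: partial response and progression | +25%: partial response and progression | partial response |

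For 30 to 45 mm: (45 - 30)/30 = +50% on baseline, but under A the reference is 45, so (45 - 45)/45 = 0%. For 40, 20, 25 mm: (25 - 40)/40 = -37.5%, and (25 - 20)/20 = +25%.

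**What follows.**

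1. With two images, readings A and B differ only for growth of 20% or more without a new lesion. Smaller growth is stable on either reading, and partial response is the same.
2. Reading B repairs the two-image case but not the interim-scan case, because the minimum is still 20 mm.
3. Reading A makes the result depend on whether an interim scan exists. The 30 to 45 mm tumour is stable without one. With an interim value of 30 mm on record it is progression, since (45 - 30)/30 = +50%.
4. Only reading C gives one category per patient in every row.

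**Modality, as a side check.** The text accepts either of two modalities and does not ask for the same one at both times. It gives no between-modality error, so any size is assumed. Take an unchanged tumour, no systematic difference, and a normal error on the log ratio with SD s. The chance of an apparent increase of 20% or more is 1 - Phi(ln 1.2 / s). That is about 0.0% for s = 0.05, 3.4% for s = 0.10 and 18.1% for s = 0.20. The range is too wide to support a claim about size. It supports recording the modality.

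**The case against.** The strongest reply is that no sensible assessor would use a scan as its own reference. The endpoint opens as a change from baseline to pre-surgery, and with two images baseline is the only usable comparator. On that reading 30 to 45 mm is progression and nothing is lost. This is fair as a prediction of practice, and it reduces the first part of the point to an ambiguity. It does not remove it. The same paragraph names the baseline sum when it means baseline, for partial response, and uses other words for progression and stable disease. Nor does it resolve the overlap when an interim scan is recorded. Such scans are not foreseen, so that part is conditional, but they are not excluded either.

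Three stronger readings are tempting, and the document does not support them.

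- A reader might infer that the endpoint cannot be scored at all. Complete response, partial response, percentage change, the size-reduction ANOVA and progression by new lesion can all be obtained from two images. For the same reason the progression category is not necessarily empty.
- A reader might infer that modality switching distorts the result. The text permits switching by silence and does not prescribe it. Its frequency is not given, and a rule may sit in a document not shown. Randomisation is stratified by hospital, so modality habits that vary by site should be roughly balanced between arms. The likely effect is noise rather than bias.
- A reader might treat the absence of imaging from the Study calendar as proof that none is planned. The calendar also omits the echocardiogram that the cardiac toxicity endpoint requires, so it is not a complete list. The two-image design rests on the endpoint definition, not on the calendar.

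**Conclusion.** The point holds in limited form. The reference stated for progressive and stable disease does not fit a comparison of one pre-treatment image with one pre-surgery image. Read literally, growth of 20% or more without a new lesion is scored as stable. With an interim scan on record, one patient can meet both partial response and progression, with no order of precedence.

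The effect is confined to the boundary between stable and progressive disease, plus the interim-scan overlap, in one secondary endpoint and its ordinal model. The primary endpoint and the sample size are untouched. The document gives neither an expected progression rate nor a frequency of interim scans, so the number of patients affected cannot be stated. The misclassification is certain only on the literal reading. Should baseline be counted in the minimum, only the overlap remains. The wording should be corrected because it is a stated rule in the endpoint definition: a later analysis document that used baseline would contradict it.

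**What to change.** Amend secondary endpoint 2 so that all four categories compare the pre-surgery image with baseline. Progressive disease becomes a sum of diameters at least 20% above baseline, or a new lesion. Stable disease becomes neither partial response nor progression against baseline. Complete and partial response stay as they are. An interim scan then has no influence on the size-based category.

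As a minor addition, record the imaging modality at both times and ask for the same modality where it is available. Keep all patients in the main intention-to-treat analysis, and add a sensitivity analysis limited to patients with the same modality at both times. Patients with mixed modalities should not be dropped from the main analysis. The pre-surgery modality is settled after randomisation, so dropping them would be a post-randomisation exclusion at odds with the intention-to-treat rule in the Statistical analysis plan section. The sensitivity analysis is supportive only, for the same reason.

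The cost is a few lines of protocol wording with the usual ethics submission, one eCRF field and one extra analysis. The price in content is that a tumour that shrinks and then regrows is classed by its net change from baseline, which is what a two-point endpoint measures. The categories should be reported as referenced to baseline.

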#### Additional measures

Attendance to the exercise sessions and adherence to the exercise prescription will be continually monitored and recorded. Sense of coherence measured by the SOC-13 scale and the Swedish version of the original Self-Efficacy for Exercise (SEE) scale will be used to better understand who adheres to and attends the exercise intervention.

Participant demographics, disease and medical history, body mass index, age, sex, education level, and smoking status will be recorded. Since this trial is not powered to assess survival and recurrence rates since follow-up will end two years after baseline. Register data will however be used in order to investigate overall and BC-specific survival rates after 2, 5 and 10 years.

## Study calendar

| ***Time point*** |  | |
| --- | --- | --- |
| Baseline (before initiation of NACT) | - Verify eligibility - Informed consent - Three 14G tumour biopsies in addition to diagnostic biopsy* - Blood and plasma samples (4-5 x 10 ml) * - Faeces samples * - Full tumour biology (ER, PR, HER2, tumour grade, and Ki67)   Baseline questionnaires and testing   1. EORTC QLQ-C30 (quality of life) 2. EORTC QLQ-B23 (quality of life, breast cancer) 3. Sense of coherence (SOC-13) 4. Godin Leisure Time Self-Reported Physical Activity questionnaire 5. Self-Efficacy of Exercise (SEE) questionnaire 6. Hand grip muscle strength test 7. 1-RM leg press test 8. Ekblom-Bak submaximal cardiorespiratory cycle test 9. Amsterdam Cognition Scan 10. BMI, body fat composition, haemoglobin levels, blood pressure, demographics and medical history | |
| **Randomization** | ***Standard*: Usual care**  ***Intervention*: Physical exercise intervention** | |
| Pre-surgery | Repeat baseline questionnaires and testing (1.-2., 4.-8., 10.)  Device-measured physical activity (Fitbit activity tracker)  Blood (4-5 x 10 ml) and faeces samples *.  Record toxicity-related outcomes and treatment details (CRF) | |
| Surgery | Breast and axillary surgery: endpoint pCR assessed and recorded.  Tumour tissue collected and stored at trial biobank* | |
| Postoperative treatment | Adjuvant treatment as per clinical routine | |
| **Follow-up (years after surgery)** | **1** | **2** |
| EORTC QLQ-C30* | x | x |
| EORTC QLQ-B23* | x | x |
| Record recurrence and survival | x | x |
| Godin (physical activity)* | x | x |
| SEE scale | x |  |
| Amsterdam Cognition Scan | x |  |
| Faeces sample * | x |  |
| Device-measured physical activity (Fitbit activity tracker) | x |  |
| Self-reported sick leave | x | x |

* Stockholm sites only

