## Monitoring and follow-up

This prospective trial is conducted according to GCP guidelines and monitored by the Clinical Trial Office at Centre for Clinical Cancer Studies, Karolinska University Hospital, Stockholm, Sweden, for Swedish sites, and further CROs in further countries participating in this trial. CROs will be monitoring inclusion and exclusion criteria as well as completeness and accuracy of data recorded in the eCRF by regular on-site visits. To this end, participating units will grant access to patient medical files in due time on request. Patients are informed about monitoring procedures and medical file access in the patient information leaflet and grant their consent to these by signing the consent form.

Each patient is followed up for two years regarding secondary endpoints. Follow-up can be conducted as telephone call or by post, and also includes access to the participant’s medical file in order to check for survival and recurrence. Follow-up must be performed within +/- two months from the surgery date, and data are to be completed in the eCRF within one month from the follow-up date. Long-term follow-up regarding survival and recurrence is conducted via national registers.

Participating sites that do not adhere to GCP guidelines or to the agreements stated in the contract signed between the medical responsible at the individual site and the Clinical Trial Office may be excluded from this trial.

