All health-related quality of life outcomes are measured as scores that range from 0 to 100, hence the outcomes are continuous. Both the global QoL score as well as the 17 subscales (8 scales reflecting symptoms and 9 reflecting function) will be assessed at four time points: baseline, pre-surgery, 1 and 2 years after surgery. To evaluate QoL scores at each time point both within and between the treatment groups, a mixed model for repeated measures (MMRM) will be used. Treatment, visit, treatment visit interaction and stratification factor biological tumour type will be included in the model as fixed effects, and patient as a random effect. An unstructured covariance matrix will be used to model the within-subject error. If the fit of the chosen structure fails to converge, the following covariance structures will be evaluated, in order, until convergence is reached: toeplitz with heterogeneity, autoregressive with heterogeneity, toeplitz, autoregressive and compound symmetry. Furthermore, differences in change from baseline between the treatment arms will be assessed at each time point by constructing relevant contrasts of the estimated regression coefficients.

1. *Self-reported physical activity*

Physical activity is reported using the Godin-Shephard Leisure-Time Physical Activity Questionnaire (GSLTPAQ) as total minutes per week of training in three intensity levels (light, moderate and intensive) and for weight training. Hence, the outcome is continuous. A mixed model for repeated measures (MMRM) will be used to assess physical activity at four different time points: baseline, pre-surgery, 1 and 2 years after surgery). The model will include treatment, visit, treatment-visit interaction and the stratification factor biological tumour type as fixed effects, and patient as a random effect. An unstructured covariance matrix will be used to model the within-subject error. If the fit of the chosen structure fails to converge, the following covariance structures will be evaluated, in order, until convergence is reached: toeplitz with heterogeneity, autoregressive with heterogeneity, toeplitz, autoregressive and compound symmetry. Physical exercise will be assessed both within and between the treatment groups. Furthermore, differences in change from baseline between the treatment arms will be evaluated at each time point by constructing relevant contrasts of the estimated regression coefficients.

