5. Sick leave is a patient-reported singular measurement at pre-surgery and at 1- and 2-year follow-up (% sick leave). Mean sick leave proportions will be compared between the treatment arms at each time point using a mixed model for repeated measures (MMRM). Treatment, visit, treatment visit interaction and the stratification factor biological tumour type will be included in the model as fixed effects, and patient as a random effect. An unstructured covariance matrix will be used to model the within-subject error. If the fit of the chosen structure fails to converge, the following covariance structures will be evaluated, in order, until convergence is reached: toeplitz with heterogeneity, autoregressive with heterogeneity, toeplitz, autoregressive and compound symmetry. Additionally, since the outcome is most likely not normally distributed, a non-parametric Kruskal-Walllis test will be performed at each time as a sensitivity analysis.
6. *Device-measured physical activity level*

Several continuous outcome measures from the Fitbit activity tracker will be assessed: 1) METs (metabolic equivalents) in low, medium and high intensity activities, respectively, 2) step counts per day and 3) daily active minutes. The main interest is to see if there is a difference between the treatment arms regarding change of physical activity from baseline to pre-surgery (i.e. after intervention and chemotherapy), but also at 1-year follow-up. A mixed model for repeated measures (MMRM) with treatment, visit and the stratification factor biological subtype as fixed effects, and patient as a random effect. An unstructured covariance matrix will be used to model the within-subject error. If the fit of the chosen structure fails to converge, the following covariance structures will be tried, in order, until convergence is reached: toeplitz with heterogeneity, autoregressive with heterogeneity, toeplitz, autoregressive and compound symmetry. Additionally, heart rates at equivalent exertion levels (assessed on the Borg scale) during physical activity will be explored.

1. *Muscle strength*

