The muscle strength is measured on a continuous score on each arm and leg. The main interest is to see if there is a change in strength after intervention, i.e. change from baseline to pre-surgery. A mixed model for repeated measures (MMRM) with treatment, visit and the stratification factor biological tumour type as fixed effects, and patient as a random effect. An unstructured covariance matrix will be used to model the within-subject error. If the fit of the chosen structure fails to converge, the following covariance structures will be tried, in order, until convergence is reached: toeplitz with heterogeneity, autoregressive with heterogeneity, toeplitz, autoregressive and compound symmetry.

1. *Cardiorespiratory fitness*

The Åstrand submaximal cycle test renders a continuous outcome. The main interest is to see if there is a change in cardiorespiratory fitness after intervention, i.e. change from baseline to pre-surgery. A mixed model for repeated measures (MMRM) with treatment, visit and the stratification factor biological tumour type as fixed effects, and patient as a random effect. An unstructured covariance matrix will be used to model the within-subject error. If the fit of the chosen structure fails to converge, the following covariance structures will be tried, in order, until convergence is reached: toeplitz with heterogeneity, autoregressive with heterogeneity, toeplitz, autoregressive and compound symmetry.

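### The study calendar contradicts the endpoint and analysis sections: late quality-of-life and activity questionnaires are limited to Stockholm, the Fitbit baseline is not listed, and the cycle test has two names

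*Protocol*

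**What the plan says.** **Questionnaires.** In the protocol's Study calendar the follow-up rows read "EORTC QLQ-C30* | x | x" and "EORTC QLQ-B23* | x | x", and the Godin row is starred in the same way. The only footnote defines the star as "Stockholm sites only". At baseline the same three instruments (items 1, 2 and 4) carry no star, and the pre-surgery row repeats them without one.

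Other sections contain no site limit:
- Outcomes, Variables and measures (items 4 and 5) sets both outcomes at baseline, pre-surgery, 1 year and 2 years.
- Under Secondary endpoints, the quality-of-life scores "will be assessed at four time points: baseline, pre-surgery, 1 and 2 years after surgery", and Godin is modelled at the same four visits.
- The Statistical analysis plan section applies intention-to-treat to all outcomes.
- Monitoring and follow-up states: "Each patient is followed up for two years regarding secondary endpoints".

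**Fitbit.** The calendar's baseline cell has ten numbered items, and Fitbit is not among them. It appears pre-surgery and at year 1. Item 7 of the endpoint list runs the device measurement from baseline to 1 year, and the analysis section places its main interest on the difference between arms "regarding change of physical activity from baseline to pre-surgery".

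**Cycle test.** The endpoint list has "Cardiorespiratory fitness assessed by the Ekblom-Bak submaximal cycle test (baseline and pre-surgery", and the calendar agrees. The analysis section says "The Åstrand submaximal cycle test renders a continuous outcome", and the synopsis also names Åstrand.

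**The concern.** The calendar is the schedule that sites work from. A coordinator outside Stockholm who applies the footnote will send no quality-of-life or Godin questionnaire at years 1 and 2. The rows for sick leave, the Amsterdam Cognition Scan, the self-efficacy scale and Fitbit are unstarred, so the same coordinator will collect those. A questionnaire missed at its visit cannot be recovered later.

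The mixed models would then be fitted to visits that are missing by design at most sites. The section on missing values expects few of them.

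The Fitbit omission carries a smaller risk of the same kind: a device baseline recorded late, or not at all, undermines a change-from-baseline analysis. The cycle-test conflict leaves the endpoint and its analysis naming different instruments.

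**Working it through.** **1. The protocol's own figure.** The only sample size derived is for pCR, 30% against 40%, two-sided 5%, power 80%, 1:1:

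n per arm = [1.960·√(2·0.35·0.65) + 0.842·√(0.30·0.70 + 0.40·0.60)]² / 0.10² = (1.322 + 0.565)² / 0.01 ≈ 356, or 712 in total.

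This reproduces the stated 712. Allowing for 10% drop-out, 712/0.9 ≈ 791, against the stated 790. The figure is not in dispute. It is used below as the number evaluable.

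**2. Visits by section.**

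| Outcome | Calendar | Endpoint list | Analysis section |
|---|---|---|---|
| Quality of life, Godin: baseline, pre-surgery | all sites | all | all |
| Quality of life, Godin: years 1 and 2 | Stockholm | all | all |
| Fitbit baseline | not listed | yes | yes (change from baseline) |
| Cycle test | Ekblom-Bak | Ekblom-Bak | Åstrand |

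**3. Size of the questionnaire loss.** The Time plan foresees 10 Swedish and 1 to 7 Finnish sites but gives no Stockholm share, so the share s is an assumption. Counting only patients with late data, the standard error rises by 1/√s. The detectable standardised difference at 80% power and two-sided 5% is (1.960 + 0.842)·√(2/m), where m = 356·s per arm.

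| Assumed share | Patients (712·s) | Late data missing | SE factor 1/√s | Detectable difference |
|---|---|---|---|---|
| 100% | 712 | 0% | 1.00 | 0.21 SD |
| 50% | 356 | 50% | 1.41 | 0.30 SD |
| 33% | 235 | 67% | 1.74 | 0.37 SD |
| 25% | 178 | 75% | 2.00 | 0.42 SD |

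The Bonferroni level in the Reporting section would raise the detectable differences in every row.

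**4. Allowing for the mixed model.** Baseline and pre-surgery scores exist at all sites, and a likelihood-based mixed model uses them. For a between-arm difference in level at a late visit, the variance factor is about (1 − R²)/s + R², where R² is the share of late-visit variance explained by the earlier scores. The protocol gives no R². With an assumed R² = 0.4:
- s = 50%: √(0.6/0.50 + 0.4) = √1.60 ≈ 1.26
- s = 33%: √(0.6/0.33 + 0.4) ≈ √2.22 ≈ 1.49
- s = 25%: √(0.6/0.25 + 0.4) = √2.80 ≈ 1.67

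The factors in step 3 are therefore upper values.

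**5. Direction of the missingness.** Randomisation is stratified by hospital, so a restriction by site removes late visits from both arms alike. The comparison within Stockholm remains randomised.

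**The case against.** The strongest reply is that the asterisks are probably a drafting slip. The other starred items are biosamples, and the endpoint list, the follow-up section and the analysis section all agree on unrestricted collection. That may be so, but nothing in the protocol tells a site to disregard the footnote.

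Several stronger readings are tempting, and the protocol does not support them:
- **No activity is measured before randomisation.** Godin is an unstarred baseline item placed before the randomisation row, so self-reported activity is collected at every site. Only the device baseline is in question.
- **No Fitbit baseline is planned.** The endpoint list plans one, and the Control section says activity in both groups is collected digitally. The fault is an omission from the calendar.
- **Site cannot enter the models.** The default adjusts for tumour type and not for site, but the protocol allows site as a random effect in the mixed models if the data permit. That could reduce bias from site differences, but it cannot replace data that were never collected.
- **The arm comparison would be biased.** Missingness would follow site and not arm, and no bias between arms has been shown. If the late effect differed between Stockholm and elsewhere, the estimate would lean towards Stockholm, which is a matter of generalisability.
- **The protocol prescribes different cycle tests at the two visits or by site.** The two sections that tell sites what to measure agree on Ekblom-Bak at both visits. The conflict is one of naming, and the planned model is the same for either continuous outcome.

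**Conclusion.** The contradictions are real and stand on the face of the text. The questionnaire asterisks matter most, because following the calendar loses data that the endpoint and analysis sections require. The loss is mainly in precision and generalisability at years 1 and 2. The complete-case standard error would rise by a factor of at most about 1.4 to 2.0 for assumed Stockholm shares of 50% to 25%. Under the mixed model the factor is smaller, about 1.26 to 1.67 if R² is 0.4. Both the share and R² are assumptions.

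The Fitbit and cycle-test conflicts are smaller and need only reconciliation. Nothing here touches pCR, its sample size or its analysis, and baseline and pre-surgery questionnaires are unaffected. This is a should-fix reconciliation.

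**What to change.** 1. Remove the asterisk from the year-1 and year-2 QLQ-C30, breast-module and Godin rows. If the restriction is intended, restate the 1- and 2-year endpoints as Stockholm-only in both Outcomes, Variables and measures and Secondary endpoints.
2. Add Fitbit to the calendar's baseline row, recorded before the exercise programme starts and, where this does not delay NACT, before allocation is known. A compulsory wear period before randomisation would go beyond reconciling the text, because the Population section asks that recruitment avoid delay.
3. Reconcile the cycle-test name across the synopsis, endpoint list, calendar and analysis section so that one test is used throughout.

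The cost is a calendar amendment and a notice to sites, two extra questionnaire mailings per participant outside Stockholm, and earlier hand-out of trackers. Follow-up by post or telephone is already allowed. With about five months of NACT and one year after surgery, the first year-1 visits fall roughly 17 months after the first participant starts treatment. The correction should be in place before then.
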